# Quzhuo tongbi formula for reducing gout flare related to uric acid lowering treatment: Study protocol for a multiple-center, randomized, double-blind, placebo, parallel-controlled clinical trial

**DOI:** 10.1371/journal.pone.0327864

**Published:** 2025-07-09

## Abstract

**Introduction:**

Gout, a prevalent metabolic rheumatic disease, arises from the accumulation of monosodium urate (MSU) crystals in joints, directly associated with hyperuricemia. Long-term or lifelong urate-lowering therapy (ULT) stands as the primary management strategy. However, there is a significant risk of gout flares during ULT, and current methods have drawbacks, including side effects. Previous research has suggested a potential benefit of the Qu-zhuo Tong-bi formula (QTF) in the treatment and prevention of gout. This study aims to evaluate the effectiveness and safety of QTF in reducing gout flares during ULT.

**Method:**

This is a multi-center, randomized, double-blind, placebo, parallel-controlled clinical trial conducted in four hospitals in Zhejiang Province, China. A total of 144 patients, aged 18–80 years, will be randomly allocated to either the intervention group (QTF + febuxostat) or the control group (placebo + febuxostat) for a 12-week treatment period. The primary outcome measure is the frequency of gout flares. Secondary outcome measures include the time from the patient’s enrollment to the first occurrence of gout flare (in days), duration of gout flare (in days), health assessment questionnaire disability index (HAQ-DI), pain level (visual analog scale – VAS), rate of achieving target uric acid levels. Occurrences of adverse events, and results from electrocardiograms and laboratory tests, will be monitored.

**Discussion:**

The findings from this study will offer valuable evidence supporting the efficacy of the QTF in reducing gout flares during ULT.

**Trial registration:**

ChiCTR20084417 Register on May 16, 2024.

## Introduction

Gout is a common metabolic rheumatic disease, and the incidence of affected individuals is increasing [1]. It is characterized by the deposition of monosodium urate (MSU) crystals in the joints, with elevated serum urate concentration (hyperuricemia) being the primary risk factor. Long-term or lifelong urate-lowering therapy can dissolve MSU crystals and reduce the body’s urate level, ultimately alleviating gout flares, making it a fundamental approach in gout management [2]. The initiation of urate-lowering therapy (ULT) is known to carry a risk of gout flares [3,4]. Studies have shown that within the first 3–6 months of starting ULT, the recurrence rate of gout flares ranges from 15% to 70% in patients with hyperuricemia and gout [5–7], potentially increasing the risk of cardiovascular events [8]. Moreover, gout, being a recurrent chronic ailment, not only causes physical discomfort for patients but also imposes a substantial economic burden [9]. Therefore, reducing gout flares is crucial when initiating ULT.

Currently, clinical practice guidelines recommend medications such as colchicine, non-steroidal anti-inflammatory drugs (NSAIDs), or corticosteroids for the management of gout flares during ULT [10]. However, colchicine is associated with significant gastrointestinal, hepatic, and renal toxicity and may potentially suppress bone marrow, necessitating caution [11–13]. Prolonged use of NSAIDs and corticosteroids can lead to serious complications, including gastrointestinal ulcers, which may impact patient adherence to ULT. Given the potential side effects and limitations of current medication for gout prevention and treatment, there is an urgent need to explore new approaches to reduce gout flares.

Several approaches have been explored to address gout flares associated with fluctuations in serum urate levels. Canakinumab, administered in doses ranging from 50 to 300 mg as a single dose or through a 4-weekly dosing regimen over 4 months, has shown effectiveness in preventing gout flares during ULT, surpassing the efficacy of colchicine alone and demonstrating good tolerability. However, it’s worth noting that this study excluded patients with potential risks related to either treatment, which may limit the generalizability of the findings to the broader population [14]. Studies have shown that rilonacept significantly decreases the frequency of gout flares during initial ULT treatment, with a favorable safety profile. While the incidence of infections with rilonacept treatment did not exceed that of the placebo in this relatively small-scale study, there remains a possibility, as observed with other IL-1 inhibitors, of an elevated risk for specific infections [15]. Currently, some studies suggest that adopting a low-dose initiation, stepwise dose-increased ULT regimen can reduce gout flares, potentially substituting for medication-based preventative treatment strategies [16–18]. However, the open-label nature of these studies could have influenced the results [16,17]. One study may have failed to achieve its primary endpoint due to an inadequate sample size [17], while another study’s protocol required the exclusion of individuals with stage 4 or 5 chronic kidney disease, limiting the generalizability of its findings, particularly in terms of safety analysis [18]. These approaches offer enhanced efficacy and safety, compared to traditional methods, providing valuable insights for clinical treatment. Nonetheless, the inherent adverse reactions of pharmacological treatments, in conjunction with factors influencing the certainty and applicability of results, underscore the importance of exploring innovative strategies and treatment modalities.

In recent years, Traditional Chinese Medicine (TCM) has been increasingly recognized for its effectiveness [19]. When combined with chemical drugs, TCM has shown enhanced efficacy in halting disease progression compared to chemical drugs alone [20]. Research has indicated that the aqueous extract of Tongfengkang not only possesses a significant anti-inflammatory effect on gouty arthritis (GA) but also lowers blood urate concentration [21]. Previous studies conducted by our team have demonstrated that Qu-zhuo Tong-bi formula (QTF) granules are effective in reducing blood urate levels and acute gout flares, with no adverse reactions reported even after prolonged use. However, these studies did not include follow-up after treatment [22]. Despite these promising results, there remains a gap in traditional Chinese medicine (TCM) research concerning the prevention of gout flares during urate-lowering therapy (ULT). To address this gap, we propose a multi-center, randomized, double-blind, placebo-controlled, parallel-group clinical trial. This study aims to investigate whether QTF granules can reduce the frequency and duration of acute gout flares associated with ULT and prolong the time to flare. Additionally, we will address the existing research gap by including a 48-week follow-up period after treatment to evaluate the long-term effects of QTF granules. The aim is to identify a safe and effective new therapeutic medication for reducing acute gout flares in the early stages of ULT in gout patients, providing valuable insights and a foundation for TCM clinical management and novel drug development.

## Methods

### Study design

A multi-center, randomized, double-blind, placebo, parallel-controlled clinical trial will be conducted in four hospitals across the province of Zhejiang, including the First Affiliated Hospital of Zhejiang Chinese Medical University, the Second Affiliated Hospital of Zhejiang Chinese Medical University, Shengzhou People’s Hospital, and Huzhou Hospital of TCM.

This protocol adheres to the SPIRIT 2013 reporting checklist prohibit [23]. The study will also proceed according to the Declaration of Helsinki (as revised in 2013). The entire study flowchart and follow-up procedures are illustrated in Fig 1 and Fig 2, respectively.

**Fig 1 pone.0327864.g001:**
[figure not shown]
Study procedure. ^a^Observe continuously throughout the study and record when it occurs. ^b^Including the number of acute flares of gouty arthritis, the time span from randomization to the first occurrence of an acute attack, and the duration of recurrent acute gouty arthritis. ^c^Red blood cell count (RBC), white blood cell count (WBC), hemoglobin (HGB), neutrophil percentage (NEU), platelet count (PLT). ^d^Alanine aminotransferase (ALT), aspartate aminotransferase (AST). ^e^Blood urea nitrogen (BUN), creatinine (Cr), serum uric acid (SUA).Qu-zhuo Tong-bi formula(QTF).

**Fig 2 pone.0327864.g002:**
[figure not shown]
The flow diagram of the study.

### Participants

#### Recruitment.

The participant recruitment process involves primarily several key steps, including recruitment screening, and obtaining informed consent from participants. Blood, urine, and stool samples will be collected with participants’ consent for further research. The recruitment process includes the following steps: 1. Developing a recruitment plan and determining needs, advertising through various channels such as recruitment advertisements in the outpatient hall, entrances of the wards, and announcements on WeChat (a popular social platform in China). 2. Assigning doctors from each center to recruit individuals and having dedicated staff to assist participants. Participants are selected based on criteria and doctors’ clinical experience. 3. Providing detailed descriptions of the clinical trial protocol to qualified participants to ensure an understanding of potential benefits and risks.

### Patients’ eligibility and criteria

We will recruit a total of 144 participants aged 18–80. The diagnostic criteria were as follows:

Diagnosis of gout: Referring to the 2015 ACR/EULAR classification criteria for gout, with a maximum score of 23 points, a diagnosis of gout can be made when the score is ≥ 8 points [24].The TCM diagnosis of spleen deficiency dampness obstruction syndrome: T/CACM1349–2021- Group standards of China Association of Chinese Medicine. (available in Table 1)

**Table 1 pone.0327864.t001:** Differential diagnosis criteria for syndrome of spleen deficiency with dampness obstruction.

Primary symptoms and signs	1. Difficulty in joint flexion and extension
	2. Joint wandering pain
	3. > 1 joint pain
	4. feeling of fullness and oppression in the epigastrium.
Secondary symptoms and signs	1. Heaviness in the limbs
	2. Abnormal bowel movements (loose/stool/alternating between loose and hard/initially hard then loose)
	3. Decreased appetite
	4. Pale tongue
	5. Soft or thin pulse

Meeting at least 4 primary symptoms and signs or 3 primary symptoms and signs along with 2 secondary symptoms and signs would indicate a diagnosis of spleen deficiency with dampness obstruction.

### Inclusion criteria

All participants must meet the following criteria:

Meet the above diagnostic criteria and be in the gout intermission stage;TCM diagnosis indicates syndrome of spleen deficiency with dampness obstruction;Serum urate level ≥7 mg/dL (420μmol/L);Aged between 18 and 80 years (inclusive of boundary values), any gender;Having not received urate-lowering drugs such as allopurinol, benzbromarone, or febuxostat in the past month;Relief of gouty flare symptoms (VAS score = 0) for more than 1 week;Acute gout flare≥2 in the past year;Willing to undergo treatment and sign informed consent.

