### Sample size

The sample size calculation was performed using PASS (version 2021) with the “Comparison of two independent sample rates” calculation module. A power of 80% and an alpha level of 0.025 for a one-sided test and a superiority test were used. Based on a previous study by our team [22], the flare rates of acute gouty arthritis after 12 weeks of placebo treatment were 63.2%, and for the group treated with the QTF was 38.5%. Calculations yielded sample sizes of N1 = N2 = 61 for both the intervention and control groups, considering a dropout rate of 20%. In total, 144 patients with intermittent gout will be included, with 72 patients in both the intervention and control groups.

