### Randomization and blinding

A multi-center competitive stratified block randomization method was utilized. Random numbers for the multi-center group were generated using the corresponding randomization procedure in SAS software (version 9.4). These random numbers, alongside their corresponding drug codes, functioned as unique identifiers for participants. After conducting necessary baseline assessments, all eligible patients who met the inclusion criteria and signed informed consent forms will be randomly assigned to either the intervention or control group in a 1:1 ratio. The randomization design and numbers were provided by Jiangsu Famous Medicine Co., Ltd. The relevant parameters and results of the randomization scheme will be recorded by Zhejiang Chinese Medical University (the research design unit). Apart from the outcome evaluators and staff at the drug production center, all researchers and patients remained unaware of treatment allocation. The QTF granules and placebo granules were identical in odor, color, and packaging, ensuring blinding. Distribution details will be disclosed to researchers only when necessary for drug administration. Products were delivered directly to patients according to their allocation codes. In emergencies, the research design unit will promptly provide researchers with randomized numbers and treatment allocations. All participants will strictly adhere to confidentiality regulations to protect patients’ personal privacy information.

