### Outcomes

#### Primary outcomes.

The frequency of gout flares will be recorded at weeks 6, 12, 24, and 48.

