### Statistical analysis

The statistical analysis for this trial will be conducted based on the Per-Protocol (PP) and Intent-to-Treat (ITT) data, conducted by Jiangsu Famous Medicine Co., Ltd., situated in Nanjing, China. Different analysis methods will be employed depending on the type of data measurement or counting.

For the primary outcome, the number of gout flares in each group will be compared using t-tests or Wilcoxon rank-sum tests, with center effects controlled through covariance analysis. For count data, such as time span to the first occurrence of gout flares, duration of acute gouty arthritis recurrence, pain visual analog scale score, HAQ-DI, and safety analysis indicators (like routine blood tests), the same methods will be applied. Measurement data, including the recurrence rate of acute gouty arthritis and the incidence of adverse events, will be analyzed using chi-square tests or Fisher’s exact tests, with center effects controlled through binary or multinomial logistic regression analysis. All hypothesis tests in this study will be two-sided, with a significance level of 0.05. Differences will be considered statistically significant when p < 0.05. SAS version 9.4 will be used for all statistical analyses.

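### The primary flare-count comparison names center as its only adjustment factor, although past-year flare count is a plausible predictor available at screening; using it could add some precision

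*Protocol article*

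**What the plan says.** Under Inclusion criteria, the protocol article requires "Acute gout flare≥2 in the past year". It gives a floor of 2 and no ceiling.

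Under Primary outcomes, "The frequency of gout flares will be recorded at weeks 6, 12, 24, and 48".

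Under Statistical analysis, "the number of gout flares in each group will be compared using t-tests or Wilcoxon rank-sum tests, with center effects controlled through covariance analysis". Center is the only factor named for the primary comparison.

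Under Randomization and blinding, "A multi-center competitive stratified block randomization method was utilized". No stratum based on flare history is named.

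The article does not say that the exact past-year count is written down, as opposed to a confirmation that it was at least 2. It gives no figure for how well past flares predict flares during the trial.

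**The concern.** The criterion lets patients with very different flare histories into one sample, and the primary outcome is the same kind of event counted after entry. If patients differ in an underlying tendency to flare, past-year flares carry information about on-trial flares. A model that adjusts for center alone leaves that between-patient variation in the error term.

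Two things are at stake, both modest:

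- **Precision.** The interval around the treatment effect is wider than it need be. The Discussion describes the sample as small because of limited funding.
- **Chance imbalance.** With 72 patients per arm, past-year flares can differ between arms by chance. That shifts the estimate in proportion to how strongly past flares relate to on-trial flares. The standard error already allows for such shifts, but adjustment would remove part of them.

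**Working it through.** **Inputs from the article**

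- 12-week flare rates: 63.2% (placebo) and 38.5% (QTF). Source: Sample size.
- One-sided alpha 0.025, power 80%, 61 per arm, raised to 72 per arm for 20% dropout. Source: Sample size.
- Past-year flares at least 2. Source: Inclusion criteria.
- Two-sided 0.05 for all tests. Source: Statistical analysis.

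**Input not in the article:** the correlation ρ between past-year and on-trial flare counts. It is assumed below, over a range.

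**Step 1. The plan's own figure.** With unpooled variance,

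n = [p1(1−p1) + p2(1−p2)] × (1.960 + 0.842)² / (p1−p2)²
= (0.2326 + 0.2368) × 7.849 / 0.247² = 60.4, so 61 per arm.

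The stated 61 reproduces. One-sided 0.025 and two-sided 0.05 give the same n. This figure is for a flare rate, so it serves here only to calibrate the simulation.

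**Step 2. Simulation set-up.** Each patient has a yearly flare rate λ drawn from a gamma distribution (mean 2, 3 or 4; variance parameter 0.1 to 1, where a larger value means patients differ more). The past-year count is Poisson(λ), kept only if at least 2. The 12-week count is Poisson(cλ), with c set in each arm so that the share with any flare is 63.2% or 38.5%. Each trial is analyzed by a linear model on treatment alone, then on treatment plus the log of the past-year count. Center is left out, and the Wilcoxon test is not addressed.

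**Step 3. Results with one shared tendency before and during the trial.** 58 evaluable per arm (72 × 0.8 = 57.6), 1,500 trials per setting:

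| Mean per year | Variance parameter | ρ placebo / QTF | Power unadjusted | Power adjusted |
|---|---|---|---|---|
| 2 | 0.1 | 0.09 / 0.06 | 89.7% | 89.7% |
| 3 | 0.1 | 0.12 / 0.08 | 91.0% | 91.3% |
| 3 | 0.25 | 0.23 / 0.16 | 90.9% | 91.5% |
| 3 | 0.5 | 0.35 / 0.26 | 92.4% | 94.1% |
| 3 | 1.0 | 0.47 / 0.35 | 92.5% | 95.7% |
| 4 | 1.0 | 0.51 / 0.38 | 92.1% | 95.6% |

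Across all twelve settings the change in power ran from about 0 to 3.5 points.

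**Step 4. Variance reduction.** Adjustment removes roughly ρ² of the variance in each arm.

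- Top of the range: 0.51² = 0.26 and 0.38² = 0.14, average about 20%.
- Bottom: 0.09² = 0.008 and 0.06² = 0.004, average under 1%.

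Direct simulation at 61 per arm and mean 3 gave a variance ratio of 0.903 for parameter 0.5 and 0.829 for parameter 1. These equal 1/0.903 = 1.11 and 1/0.829 = 1.21 times the patients.

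**Step 5. Relaxing the shared tendency.** Flares after starting urate-lowering therapy may not follow the same tendency as flares before it. At mean 3, with the two tendencies correlated 0.5, the variance reduction falls to between about 0% and 5%. With correlation 0.3 it is about 0% to 3%.

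**The case against.** **The article condenses a fuller plan.** A list of covariates is usually settled in the statistical analysis plan, which is not shown, and the article does not say that center is the only covariate allowed. Likewise, it calls the randomization stratified without listing the strata. This is fair, and the silence alone would be no finding. What stands is that the article commits to a primary comparison, names a covariance adjustment and names center in it. A better-specified model can be put beside that statement at small cost.

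**A reader might infer that a strong predictor is collected and then ignored.** The documents do not support either half. No figure shows that past flares predict strongly. The criterion is met by confirming at least two flares, so the exact count may not be on file, and the fix may need new data.

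**A reader might infer that the primary result would be biased or the type I error inflated.** It would not. Allocation is randomized, and the unadjusted comparison remains valid.

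**The gain may be close to nothing.** Entrants have been off urate-lowering drugs for at least a month, and the article describes flares as a risk of starting them. If the two tendencies differ, little variance is removed. This stands, and it is why the range starts at zero. Simulated power is also already about 90% or more, so the main benefit is a narrower interval.

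**Conclusion.** The point holds as an efficiency improvement, not as a validity defect. As written, the primary flare-count comparison adjusts for center alone and leaves unused a plausible baseline predictor that can be established at screening.

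The size is uncertain because the article gives no correlation. Under gamma-Poisson assumptions calibrated to its 12-week rates, adjustment cuts the variance of the treatment effect by about 0% to 20% and adds about 0 to 3 points of power. The upper end needs wide differences between patients and one tendency to flare that carries over unchanged from the past year into the trial. If that link is weak, the gain is a few percent at most. No setting showed a loss beyond simulation error.

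**What to change.** 1. Record the actual number of flares in the past year on the case report form before randomization. For patients already enrolled, take it from screening notes.
2. Before unblinding, amend the Statistical analysis section so that the primary analysis is a covariance model for the flare count with treatment, center and the log of the past-year count. This model should replace the unadjusted t-test or Wilcoxon test as primary.
3. Optionally, use the same covariate in the logistic model for the recurrence rate, and state that the odds ratio is then conditional on flare history.

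The cost is one form field, a short change to the analysis text, and retrieval of counts for patients already enrolled. Recall error in the count reduces the gain. Because the count refers to the time before randomization, such error does not bias the treatment comparison, provided that retrieval is done blind to allocation.

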### Exclusion criteria

Patients meeting any of the following criteria will be excluded:

Severe liver or kidney dysfunction (AST/ALT ≥ twice the normal level, eGFR < 60ml/min), diabetes with target organ damage, severe cardiovascular or cerebrovascular diseases, history of digestive ulcer bleeding or perforation, and patients with psychiatric disorders;Patients’ intolerance to or with contraindications to the medications used in this study (urate-lowering medications, traditional Chinese medicine, nonsteroidal anti-inflammatory medications);Patients with hyperuricemia caused by myeloproliferative disorders or other conditions with obvious urate overproduction;Pregnant or lactating patients.

### Exit criteria

#### 1. Investigator-initiated exit.

Exiting the trial refers to situations where enrolled subjects encounter circumstances during the trial that make it inappropriate for them to continue participating, as determined by the investigator. These circumstances may include 1) Poor subject compliance (< 80%), concurrent use of medications outside the protocol, or discontinuation of treatment measures midway through the trial by the subject; 2) Poor patient compliance (medication compliance <80% or >120%), self-initiated medication changes, or additions of medications concomitant medicationed by the protocol; 3) Unblinding midway due to various reasons; 4) Occurrence of certain complications, adverse events (AEs), or special physiological changes during the trial, judged by the physician as unsuitable for continued treatment, leading to withdrawal; 5) Allergic reactions or severe AEs occurring during the trial, leading to trial termination based on physician judgment.

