During the treatment period, in the event of gout flares, patients are advised to rest in bed with the affected limb elevated. Within 24 hours, they are required to contact the research personnel for a Visual Analog Scale (VAS) pain assessment: mild (VAS score < 5), moderate (5 < VAS score < 8), severe (VAS score > 8). Early administration of an adequate dose of NSAIDs is recommended within 24 hours. In this study, it is specified as a once-daily administration of 120 mg of etoricoxib (with an onset of action within 1 hour and a half-life of approximately 22 hours), with dosage reduction upon relief of symptoms. Blood and urine samples are collected from patients who consent for further research purposes. In the case of AEs, the use of QTF granules or placebo granules is temporarily suspended until the condition stabilizes.

The observing physician will meticulously record the quantity of medication received, used, and returned by the participants to assess medication adherence and ensure timely documentation in the case report forms. Based on the participant’s adherence, a decision will be made regarding their continued participation in the trial. The exclusion criteria for poor adherence are medication adherence rate = (actual medication amount/ theoretical medication amount) < 80% or > 120%. The medication administrator is responsible for locking the cabinet, sealing the medications, and storing them at room temperature. If a participant withdraws from the study early, any remaining medication should be collected and returned.

Regulations on Concurrent Treatments: During the trial, the use of various anti-rheumatic drugs, muscle relaxants, and analgesics, including both traditional Chinese and Western medicines such as Shenling Baizhu Powder/ Pills and Pingwei Powder, is generally prohibited. Additionally, physical therapies such as massage and acupuncture are not allowed.

If participants need to continue taking other medications or undergoing other treatments due to concurrent diseases, these must be documented in detail in the concurrent medication log.

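### The exit rules let investigators end trial participation, not only the granules, for post-randomization reasons with no stated follow-up, which weakens the planned ITT analysis

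*Protocol article*

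**What the plan says.** The Exit criteria (Investigator-initiated exit) concern leaving the trial, not stopping the granules. They cover circumstances that "make it inappropriate for them to continue participating, as determined by the investigator. These circumstances may include" a list of five items:

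- "Poor subject compliance (< 80%), concurrent use of medications outside the protocol, or discontinuation of treatment measures midway through the trial by the subject"
- "Poor patient compliance (medication compliance <80% or >120%), self-initiated medication changes", so adherence appears twice in one list with different limits
- "Unblinding midway due to various reasons"
- complications or adverse events "judged by the physician as unsuitable for continued treatment, leading to withdrawal"
- allergic reactions or severe adverse events, again on the physician's judgment.

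The Intervention section repeats the link: "Based on the participant’s adherence, a decision will be made regarding their continued participation in the trial". It defines adherence as actual over theoretical amount, with limits of 80% and 120%. It also says: "In the case of AEs, the use of QTF granules or placebo granules is temporarily suspended until the condition stabilizes". Analgesics and anti-rheumatic drugs are generally barred, but etoricoxib is specified for flares.

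Granules are given for 12 weeks. The primary outcome, flare frequency, is recorded at weeks 6, 12, 24 and 48. The Statistical analysis section states: "The statistical analysis for this trial will be conducted based on the Per-Protocol (PP) and Intent-to-Treat (ITT) data". It compares numbers of flares by t-test or Wilcoxon rank-sum test. The article nowhere says that flares are still recorded once a patient has exited.

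**The concern.** Stopping a treatment and leaving a trial are different events, and an ITT analysis needs them kept apart. Here adherence, other medication, stopping treatment, unblinding and adverse events are all grounds for ending participation. All of them arise after randomization, and some can follow from the outcome or from tolerability. A patient in pain may take a barred analgesic or anti-rheumatic drug other than etoricoxib; a patient with side effects may stop or miss doses.

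If recording then ceases, later flares are not counted, for reasons that may differ between arms. A plain comparison of flare counts would favour whichever arm has more or earlier exits. Being off granules is no reason to stop recording, since by design every patient is off them from week 12 to week 48. The Subject-requested exit paragraph points the same way: it treats failure to finish the course as withdrawal and acknowledges that the data are then incomplete.

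**Working it through.** **1. The plan's own figure, for scale.** Inputs from Sample size: 63.2% v 38.5%, one-sided alpha 0.025, power 80%. Unpooled formula: n = [p1(1−p1) + p2(1−p2)] × (1.960 + 0.842)² / (p1−p2)² = 0.4694 × 7.849 / 0.0610 = 60.4, so 61 per arm, as stated. With 72 per arm the expected difference in patients with a flare is 72 × 0.247 = 17.8. The planned 20% dropout is 0.20 × 144 = 28.8 patients, more than that contrast.

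**2. How easily the adherence limit is reached.** A full course is 12 weeks × 5 days × 2 = 120 sachets; 80% is 96. Missing more than 24 sachets, that is more than 12 dosing days or 12/5 = 2.4 weeks, puts a patient below 80%. A suspension longer than this for an adverse event would do so by itself if the suspended doses stay in the theoretical amount, and would not if they are removed. The text does not say which.

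**3. Follow-up at risk.** Exit by week 12 loses at least 48 − 12 = 36 weeks, or 36/48 = 75% of the recording period.

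**4. Truncated counts with no true effect.** Assumptions: constant and equal flare rate, a fraction e of an arm exits at week t, and flares before exit are kept. The mean recorded count is then the full mean × [1 − e(1 − t/48)]. Entries are the QTF/control ratio of mean counts; the true ratio is 1.

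| Exit week | Share lost | Exit 20% both arms | Exit 10% control, 30% QTF | Exit 30% control, 10% QTF |
|---|---|---|---|---|
| 6 | 0.875 | 1.00 | 0.7375/0.9125 = 0.81 | 1.24 |
| 12 | 0.750 | 1.00 | 0.775/0.925 = 0.84 | 1.19 |
| 24 | 0.500 | 1.00 | 0.85/0.95 = 0.89 | 1.12 |

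The spurious change runs from a 19% reduction to a 24% increase, and is nil when exits are equal. If flares cluster early, less is lost; if those who exit are more flare-prone, more is lost. Ranks shift in the same direction as means.

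**5. Exited patients left out altogether, as in a PP or complete-case analysis.** Assumptions: true flare rate 63.2% in both arms, 20% exit per arm. Observed rate = (0.632 − 0.20f)/0.80, where f is the flare risk among those who exit.

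- f = 63.2% in both arms: no difference.
- f = 63.2% control, 90% QTF: 63.2% v 56.5%, a false 6.7 points; one-sided false-positive rate about 11% instead of 2.5%.
- f = 40% control, 90% QTF: 69.0% v 56.5%, a false 12.5 points; about 28%.

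Swapping the arms reverses the sign.

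**6. Power when everyone is followed (two-proportion test on flare rate, pooled).** With 72 per arm and no dilution: 85.0%. If 20% of the QTF arm has the placebo risk (assumption), its rate is 0.8 × 38.5 + 0.2 × 63.2 = 43.4% and power is about 66%. If instead 20% are left out, 57.6 per arm give 76.2%, before any bias.

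**The case against.** A reader might infer that these patients are removed automatically. The text does not say so: exit is for the investigator to determine, the list is of circumstances that may apply, and the Intervention section speaks of a decision. Missing more than 24 sachets opens that judgment; it does not settle it. This stands, although discretion is not a safeguard, since it can be used differently across four centers.

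A reader might also infer that ITT cannot be done. That is wrong. All randomized patients can be analysed as allocated, using data up to exit and a missing-data method that an unseen SAP may give. But no method recovers flares that were never recorded.

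Nor are flaring patients lost simply because they flared. Etoricoxib for a flare is within the protocol, and patients must contact the study within 24 hours of a flare, so the flare that led to exit should be on record. First flares and the 12-week flare rate would then be largely intact for those patients; mainly later flares are lost. Exits for tolerability, adherence or unblinding lack this protection.

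The exit rates above are invented, and a large imbalance in a double-blind trial with no effect is not shown to be likely. That also stands: step 4 shows a mechanism, not a forecast. The full protocol may provide follow-up after exit. Even so, the published wording ends trial participation, and that wording needs correcting. Which analysis set decides may be settled in the SAP, so its absence here is not counted as an error.

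**Conclusion.** The concern holds in limited form. As written, the plan permits trial participation to end for post-randomization reasons that can be linked to flares or tolerability, states no follow-up after exit, and still intends ITT with the primary outcome recorded to week 48. This undermines the ITT analysis without preventing it. What is firm is arithmetic on the plan's own figures: at least 36 of 48 weeks are at risk for an exit by week 12, and more than 24 of 120 missed sachets puts a patient under the 80% limit. The size and direction of any bias rest wholly on assumed exit rates and timing, and are zero if exits are balanced and unrelated to flares. The Exit criteria and Intervention sections must be reconciled on adverse-event suspension and on the two adherence limits. The change is worth making before more follow-up is lost, because it is cheap and unrecorded flares cannot be recovered afterwards.

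**What to change.** Amend the Exit criteria, Intervention and Statistical analysis sections together:

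- Define stopping study granules and leaving the trial as separate events, with separate reasons recorded.
- Keep scheduled visits and flare recording to week 48 for all randomized patients, whatever their adherence, other medication, treatment status or unblinding, unless consent is withdrawn.
- Use the 80% and 120% limits, stated once, only to define the PP set, and state whether doses withheld during an adverse-event suspension count in the adherence ratio.
- Name ITT (all randomized, as randomized) as primary and PP as supportive, if the SAP does not already do so.

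Decisions to stop or suspend treatment stay with the physician; nothing here alters them.

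The cost is amendment wording, a site instruction, and some contacts with patients off granules at visits already scheduled, the last of them by phone or WeChat. The statistical price is some dilution of the effect estimate, and with it power, as in step 6 of the working. That dilution is part of the effect that an ITT analysis sets out to estimate.
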